### Sample size

As CHO-CAP was designed and executed in parallel to the CAPiTA study, the sample size is - to a large extent – determined by the infrastructure of that study. The sample size of the different cohorts in CHO-CAP is determined by the expected number of CAP episodes occurring in the CAPiTA trial (i.e. ~ 2,000 cases, see [1]), as well as by the response rate obtained for the baseline CHO-CAP questionnaire and the willingness of patients with CAP and controls to participate in the nested matched cohort study. It is expected that at most 600 CAP episodes will be included in the “diseased” cohort and 1,200 controls in the “non-diseased” cohort.

### Data analysis

#### Descriptive statistics

The health status as observed in the baseline cohort and at different follow-up moments in the “diseased” and “non-diseased” cohorts will be presented, with and without stratification for age, gender and/or baseline EQ-5D scores. Following guidelines from the SF-36 developers [24,25], SF-36 results will be presented in a decomposed manner, i.e. for the 8 sub-scales and for the 2 composite summary scores for physical and mental functioning. We will calculate mean, median and the 5th, 25th, 75th and 95th percentiles for all QoL data.

The observed use of healthcare and other resources for CAP patients and controls over time will be described, in quantity (volumes of resource use) and in costs, following Dutch guidelines for health economic studies [26]. Costs will be presented, both undiscounted and discounted using different discount rates. Decomposed in volumes of resources use and associated costs, results will be presented as mean, median and the 5th, 25th, 75th and 95th percentile.

#### Statistical analysis

The main analysis will be the comparison of the matched cohort of CAP patients with the non-diseased controls. Univariate analysis will be applied in first instance. Depending on the distribution of data, we will use t-test or non-parametric tests (e.g. nonparametric bootstrap) to estimate the difference between both cohorts. Univariate analysis is also applied when analysing the health status for age groups within the baseline population. Here, ANOVA tests will be used as well. Where dealing with mainly normally distributed data, OLS (Ordinary least squares) regression is applied. Otherwise, the generalized linear model (GLM) will be preferred.

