#### Nested matched cohort study

As part of the CAPiTA trial, patients with a clinical suspicion of CAP are tracked in 56 Dutch sentinel hospitals. The duration of follow-up within CAPiTA is defined by the number of primary endpoints captured (i.e. 130 first CAP episodes caused by vaccine-type *S. pneumoniae* serotypes). It is expected that around 2,000 CAP episodes will occur within the study population [1]. Assuming a response rate of ~30%^a^ for the baseline questionnaire, we expected approximately 600 first CAP episodes among CHO-CAP participants. Local research nurses in sentinel hospitals notify the CHO-CAP team of newly admitted CAPiTA patients with a clinical suspicion of CAP directly after hospital admission and at the time of discharge. After discharge, eligible patients (i.e. CHO-CAP participants) will be asked to participate in the prospective cohort study for a period of one year. Patients are informed (orally and by written information) that participation involves one interview during a home visit, with three subsequent questionnaires to be completed during the 12 month period. Patients again provide informed consent upon inclusion in the prospective cohort study. Exclusion criteria for the prospective cohort study are hospitalization for a second (or further) hospitalization for CAP related complaints, inability to complete questionnaires, or a recent diagnosis of malignancy as the study was considered too burdensome for this latter group.

For each patient with CAP in the prospective cohort study (“diseased” cohort), two matched unaffected subjects (i.e. no CAP episode until the time of matching) will be selected from the baseline population for inclusion in the “non-diseased” cohort (see Figure 1). Matching is based on age (same age, with allowance of 3 years age difference), gender and baseline health status (same EQ-5D score [22], with maximum allowance of 5 percent points difference). Expectations are that both in the short-term and the medium term, CAP patients consume more medical resources, require more (in)formal help, might experience more trouble to get back to their daily activities, and have a lower quality-of-life than their non-diseased peers. Furthermore, mortality, both within-hospital as during the 12 months follow-up period, is expected to be higher in CAP patients than in controls.

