a) Questionnaires (in Dutch) are available on request from first author.

b) n.a. = not applied.

Similar procedures are followed for the controls. An identified and eligible control who expressed interest to participate at the time of vaccination is visited at home. If consent is given, a questionnaire similar to that administered in the “diseased” cohort is provided (see details in Table 2).

In both the “diseased” and “non-diseased” cohorts, further data is collected on 1, 6 and 12 months after the initial home visit. Questionnaires are send by post, with the request to fill-in and send back within a week. If no response is received, participants are contacted by phone. This follow-up questionnaire addresses current living conditions, quality-of-life, co-morbidities and healthcare resources used (Table 2). A new diary for recording of healthcare use and other out-of-pocket expenses in the forthcoming period is provided once the questionnaire has been returned.

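### The main test is chosen by the observed distribution and is tied neither to the 1:2 matching nor to a mean cost difference

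*Protocol article*

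**What the plan says.** The Statistical analysis section defines the main comparison: "The main analysis will be the comparison of the matched cohort of CAP patients with the non-diseased controls". The order of work follows: "Univariate analysis will be applied in first instance". The choice of test comes next: "Depending on the distribution of data, we will use t-test or non-parametric tests (e.g. nonparametric bootstrap) to estimate the difference between both cohorts". Regression is chosen by the same criterion: "Where dealing with mainly normally distributed data, OLS (Ordinary least squares) regression is applied", and then "Otherwise, the generalized linear model (GLM) will be preferred". No covariates, matched-set term or resampling unit are named.

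The design is described under Nested matched cohort study. For each patient, "two matched unaffected subjects (i.e. no CAP episode until the time of matching) will be selected from the baseline population". On the factors: "Matching is based on age (same age, with allowance of 3 years age difference), gender and baseline health status", with EQ-5D allowed to differ by at most 5 percentage points. That section also expects mortality over the 12 months to be higher among patients than controls. It offers the second control partly as protection against loss to follow-up.

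After the home visit, "further data is collected on 1, 6 and 12 months after the initial home visit". The Descriptive statistics section reports costs as means, medians and percentiles. The Abstract gives the purpose as finding the extra cost and quality-of-life change due to pneumonia, and the Discussion says the data will serve cost-effectiveness models.

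**The concern.** Matching is the core of this design, yet the rule for the main analysis turns on a different question, namely the shape of the data. Three consequences follow if the rule is applied as a simple comparison of two cohorts.

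- **Precision.** Matching on factors that predict the outcome makes members of a set alike. An analysis that disregards this reports intervals that are too wide, in a study whose size is capped by the parent trial.
- **Balance.** Matching balances the cohorts only while sets stay intact. If a frail patient dies or withdraws and both controls remain, the remaining patients have better baseline health than the remaining controls. An unadjusted difference would then understate the quality-of-life loss. A second control does not help when it is the patient who is lost.
- **Target.** Costs are usually skewed, so the rule points them towards a non-parametric test. If that were a rank test, it would address a different quantity from the mean excess cost.

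**Working it through.** **The plan's own figures.** 2,000 expected episodes × 0.30 = 600 patients, and 600 × 2 = 1,200 controls. Both match the Sample size section. No alpha, power, effect size or SD is stated, so there is no power figure to reproduce.

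**Precision.** Inputs: 600 complete sets at 1:2 (article); outcome SD s and a common within-set correlation rho (rho is assumed, as the article gives none). For one set, the variance of patient minus mean of two controls is

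s²[1 + (1 + rho)/2 − 2·rho] = 1.5·s²·(1 − rho).

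Over 600 sets the true variance is 1.5·s²·(1 − rho)/600. An analysis that disregards the sets uses s²(1/600 + 1/1,200) = 1.5·s²/600, so its SE is 0.0500 s whatever rho is. The ratio of the two SEs is 1/√(1 − rho).

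| rho (assumed) | true SE (in s) | SE if sets are ignored | excess | coverage of nominal 95% interval |
|---|---|---|---|---|
| 0 | 0.0500 | 0.0500 | 0% | 95.0% |
| 0.1 | 0.0474 | 0.0500 | 5% | 96.1% |
| 0.2 | 0.0447 | 0.0500 | 12% | 97.2% |
| 0.3 | 0.0418 | 0.0500 | 20% | 98.1% |
| 0.4 | 0.0387 | 0.0500 | 29% | 98.9% |

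Coverage is 2Φ(1.96/√(1 − rho)) − 1. The error is conservative. The percentage excess does not depend on the number of sets, so it also holds if fewer than 600 patients are enrolled.

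**Balance after loss.** All inputs here are illustrative: baseline EQ-5D SD 0.2, roughly normal; slope of later on baseline utility 0.6; patient retention p_low and p_high in the lower and upper half of baseline EQ-5D; no selective loss in controls. The mean of each half lies 0.798 SD from the centre, so the baseline mean of retained patients shifts by

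0.798 × 0.2 × (p_high − p_low)/(p_high + p_low).

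- Retention 70%/90%: 0.1596 × 0.2/1.6 = 0.020; × 0.6 = 0.012 utility.
- Retention 60%/90%: 0.1596 × 0.3/1.5 = 0.032; × 0.6 = 0.019 utility.

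The shift favours the patients, so it makes the loss look smaller.

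**Target of a rank test.** Lognormal costs were simulated with equal means, 600 patients with log SD 1.0 and 1,200 controls with log SD 1.5 (assumed shapes; 1,000 runs; 5% level). Mann-Whitney rejected in about 100% of runs and Welch's t-test in 8%. With log SD 1.0 in both groups the figures were 4.2% and 4.4%. A rank test can therefore signal a difference where mean costs are identical.

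**The case against.** The strongest reply is that the article nowhere says unpaired. It says t-test, directly after calling the comparison matched. A one-sample t-test on patient minus mean of two controls is a t-test, and a bootstrap can resample sets. OLS or GLM could carry the three matching variables. A condensed article commonly leaves such detail to the full protocol or analysis plan. This stands in part: a reader might infer that an unpaired test is specified, and the text does not support that.

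A reader might also infer that the repeated visits will be treated as independent observations. That would matter: with three visits correlated 0.3 to 0.7, the true SE is √(1 + 2r) = 1.265 to 1.549 times the reported one. But nothing says visits will be pooled. Results at the different follow-up moments suggest visit-by-visit comparisons, whose SEs need no person effect, and total 12-month cost is one value per person.

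Other parts of the reply also hold. The precision error is conservative and vanishes at rho = 0. The dropout figures rest on assumed rates, and similar selective loss in controls would shrink them. The only non-parametric example named is the bootstrap, which suits a mean, and mean costs are reported, so a rank test is left open rather than planned.

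What the reply does not remove is the stated rule itself. Letting the observed distribution choose the main test is written in the article, not left out of it. That rule sits beside a design whose sets are expected to be broken by mortality and loss to follow-up.

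**Conclusion.** The point holds in a limited form. The article fixes the main test badly: the distribution selects it, and none of the named methods is tied to the matched sets, the matching factors or a mean cost contrast.

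- If the sets are disregarded, the SE is 0% to 29% too large for assumed rho of 0 to 0.4. This is lost precision, not a raised false-positive rate.
- Imbalance after selective loss of patients is plausible from the article's own expectations. Its size cannot be derived from the article; 0.012 to 0.019 utility is an illustration only.
- A rank test for costs is possible under the wording but not stated. It would not answer the study's cost question.

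The expected cohort sizes are consistent with their inputs and are not in question.

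**What to change.** In the Statistical analysis section, replace the distribution-driven choice with primary contrasts set in advance:

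- **Quality of life:** the mean difference at each visit from a regression adjusted for age, gender and vaccination-time EQ-5D, with clustering by matched set. Add a person effect if visits are modelled jointly.
- **12-month cost:** the arithmetic mean difference from adjusted OLS or a GLM whose family and link allow zero costs. Take 95% intervals from a bootstrap that resamples whole matched sets.
- **Rank tests:** none for the primary contrasts.

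The adjustment variables are already held in the study databases, so no new data or patient burden is involved. The cost is revised wording, slightly more analysis work and some model dependence. Adjustment corrects imbalance on the matching factors only. It does not correct for unmeasured frailty, and it does not settle how deaths enter the comparison.

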## Discussion

The infrastructure of the CAPiTA trial offers a unique opportunity for prospective collection of health outcomes, QoL and cost data of patients hospitalized with CAP. Such data will facilitate the construction and validation of health economic models on cost-effectiveness and cost-utility of 13vPnC in the future, should this become necessary if vaccine efficacy and safety is demonstrated.

One of the limitations of the current study is that we might mainly reach the ‘healthier’ part of the community-dwelling CAPiTA participants, as older and more diseased subjects may be less willing to participate in additional research projects next to the main CAPITA trial. To gain insight into this possible bias, we will compare the baseline demographic data of the CHO-CAP cohort population with the larger CAPiTA population. Further, data gathered within the CAPiTA-study will enable us to compare CAP cases from the current CHO-CAP cohort with all CAP cases, for instance with regard to duration of hospitalization and occurrence of complications.

With an expected 600 CAP episodes we expect to constitute one of the biggest prospectively studied cohorts of hospitalized elderly with CAP with regard to resources use and QoL data. Strengths of this study further include collection of out-of-pocket costs of patients and productivity losses of both patients and their caregivers and the follow-up period of up to one year post-discharge. Our study is expected to add more in-depth knowledge on the short and longer term outcomes of pneumonia in elderly.

## Endnote

^a^Commercial marketing questionnaires without any involvement of the participants normally reach a response rate around 20%. Healthcare questionnaires are known to obtain slightly higher response rates, whereby the greater the involvement, the higher the response rate. Given their previous participation in the CAPiTA study we expected some involvement from these participants for the current study, and therefore a response rate of 30% was expected to be feasible.
